A systematic Cochrane Review of fluoride varnish application (Marinho et al. [9] concluded that this treatment reduced worsening of caries (known as a 'prevention fraction') in the primary dentition by 33 %, as measured by the 'd_3_mfs' score for deciduous teeth (number of decayed (at the dentine level), missing and filled surfaces). At the 'd_3_mft' level (decayed missing and filled teeth), the amount of prevented disease was possibly larger with an estimate of 53 %. Most of the studies included in the review were from populations with regular use of fluoride treatments, especially toothpaste.

On the one hand it is known that many deprived children in Scotland have not been using fluoride toothpaste in the past, but on the other hand the Childsmile programme should be addressing this problem. Perhaps a 33–53 % reduction in worsening of dmfs/dmft is a reasonable estimate of how much fluoride varnishes could achieve in a deprived population in the West of Scotland. However, the Cochrane review was only based upon nine trials, and only two of these looked at the deciduous teeth of 3 and 4 year olds. The 'numbers needed to treat' varied from 3.7 in low caries populations to 1.6 in higher caries populations.

A number of relevant studies have been published since the 2002 review. A randomised controlled trial by Skold et al. [21] involved Swedish schoolchildren being assigned different frequencies of varnish treatment, across three different levels of dental risk including a 'high risk' group. This study demonstrated a prevention fraction for varnish at six-monthly intervals of 69 % in high risk areas, 66 % in medium risk areas, and only 20 % in low risk areas. Although of great interest the study is of secondary school children aged 13 to 16 years, so does not answer the specific questions addressed in the present study. A German study reported by Borutta et al. [4]) appears to be closer to the proposed study. The aim was to assess the caries inhibition effect of fluoride varnishes among preschool children with high caries risk though an examiner-blind, clinically controlled 2-year study with 200 randomly selected 2- to 4-year-olds. As with the present study, four varnish applications were offered. The study reports a caries reduction level of 57 % for the fluoride varnish compared with controls. However there is no reference to the study taking place within an established prevention programme as represented by Childsmile Nursery in the present study.

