### Study outcome measures

#### Primary outcome measure

The primary outcome measure is d_3_mft at 2 years of follow up compared to the d_3_mft at baseline (d_3_mft is dental decay as measured by the number of: teeth affected by decay into the dentine; missing teeth; and filled teeth).

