### Statistics and data analysis

#### Statistical analysis plan

The study will have a comprehensive Statistical Analysis Plan, which will govern all statistical aspects of the study, and will be authored by the trial statistician and agreed by the Trial Management Group (TMG) before any unblinded data is seen.

Binary endpoints such as evidence of any new decay will be analysed by Mantel-Haenszel Chi-squared tests and odds-ratios, with the attendant 95 % confidence intervals. This type of analysis will also be carried out on safety event data. Changes in d_3_mft will be analysed by Wilcoxon tests, unless these changes are normally distributed and therefore suitable for analysis by Analysis of Covariance. Compliance will be compared with a chi-squared test. The subgroup analyses will be carried out for the primary endpoint using logistic regression with interaction terms between treatment and subgroup. All statistical tests will be two-tailed tests at the 5 % significance level. There should be no concerns regarding multiple testing. All randomised controlled trials examine secondary endpoints to examine consistency of results and to generate hypotheses for further research.

All analyses will follow the intention to treat principle [8, 11]. Study subjects will be analysed in their randomised groups regardless of the treatment actually received. Also, subjects who violate the rules of the study (‘protocol violators’) will be included in all of the analyses, provided that the 2 year endpoint data has been recorded. Ideally an intention to treat analysis would be carried out on all of the randomised subjects, but there is usually some missing primary endpoint data that prevents this. We will also carry out a ‘Worst Case Analysis’ of the Primary Endpoint. In this analysis the missing endpoints will be assumed to be treatment failures, e.g., ‘new decay’.

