#### Primary efficacy analysis

The primary outcome measure is d_3_mft at two years of follow up compared to the d3mft at baseline (d_3_mft is dental decay as measured by the number of: teeth affected by decay into the dentine; missing teeth; and filled teeth). The primary analysis is the comparison between the treatment groups in percentages of children experiencing new decay as defined by the primary endpoint, namely an increase in d_3_mft.

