#### Secondary efficacy analysis

Secondary analyses will be of:absolute change in d_3_mft at 2 years of follow up minus the d_3_mft at baseline,absolute change in d_3_mfs at 2 years of follow up minus the d_3_mfs at baseline.

We will do pre-defined subgroup analyses on the following types of subgroup:children with pre-existing disease, children without pre-existing disease,we will attempt to split the children into areas that are ‘extremely’ deprived and only ‘very deprived’ based on the SIMD of the child’s postcode.

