#### Sample size

Assuming that prevalence data on childhood caries development in the recent literature are roughly applicable, if none of the 3 year olds with existing disease had ‘worsened’, then 24.65 % (57.63–32.98 %) would have experienced new decay. If all of the 5 year olds with decay had worsened then 57.63 % could have experienced new decay. The half-way point between these minimum and maximum percentages is therefore 41.14 %. We therefore roughly estimate that 41 % of 3 year olds will experience new decay over the course of 2 years of follow-up.

In the study of older children by Skold et al. [21] it was found that 6 month treatment by fluoride varnish for 3 years reduced the development of new caries or lesions by 54.7 % in the high risk group (75 % new decay for controls versus 34 % in the varnish group). If we multiply 54.7 % by two thirds to roughly approximate the effect of following up for 2 years rather than 3 years we would get a reduction of around 36.5 % in the development of new lesions or caries.

A 36.5 % reduction from 41 % would equal 41–41%x0.365 = 26.035 %. However, the Skold study was carried out in much older children with greater levels of decay, and our treatment will be nested within a public health intervention that includes provision of fluoride toothpaste. If we took a more cautious approach to the effect size of the treatment we could compare a 41 % worsening in the control group to a 31 % worsening in the treatment group (a 24 % reduction).

A two group chi-squared test with a two-sided significance level of 0.05 will have 90 % power to detect the difference between a Group 1 proportion of 0.41 and a Group 2 proportion of 0.31 (an odds ratio of 1.55) when the sample size in each group is 483. We therefore need a total of 966 evaluable subjects. Allowing for a pessimistic dropout rate of 40 %, we would need to randomise 805 subjects in each of the two groups, giving a total number of 1610 subjects to be randomised.

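### The normality switch for change in d3mft will in practice always select an unadjusted, unstratified Wilcoxon test; drop it, stratify the test, and pre-specify a baseline-adjusted mean difference

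*Protocol article*

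**What the plan says.** The rule is in the protocol article under Statistics and data analysis, Statistical analysis plan. Changes in d3mft are to be analysed by "Wilcoxon tests, unless these changes are normally distributed and therefore suitable for analysis by Analysis of Covariance". No stratification is named for the Wilcoxon test and no effect measure for the change. In the same paragraph, binary endpoints get "Mantel-Haenszel Chi-squared tests and odds-ratios, with the attendant 95 % confidence intervals".

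The rule serves a secondary endpoint. Secondary efficacy analysis lists "absolute change in d_3_mft at 2 years of follow up minus the d_3_mft at baseline" and, next to it, "absolute change in d_3_mfs at 2 years of follow up minus the d_3_mfs at baseline"; the rule names only the first. The primary analysis is a separate binary one, the "comparison between the treatment groups in percentages of children experiencing new decay as defined by the primary endpoint, namely an increase in d_3_mft".

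Four other statements bear on the point:

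- The score counts "teeth affected by decay into the dentine; missing teeth; and filled teeth", so it takes whole numbers (Primary outcome measure).
- The planning rates are a "41 % worsening in the control group to a 31 % worsening in the treatment group" (Sample size).
- Children enter with or without existing cavities (Inclusion criteria), and allocation is blocked within each nursery (Study population).
- The alternative hypothesis is worded as a smaller rise in d3mft in the varnish arm (Study rationale – hypothesis). The Background suggests that a 33–53% reduction in worsening of dmfs/dmft "is a reasonable estimate of how much fluoride varnishes could achieve in a deprived population".

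**The concern.** The rule appears to offer two analyses, but the planning figures leave only one. With most children showing no increase on a whole-number scale, the change cannot look normal, so the analysis-of-covariance branch is a dead clause.

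The stated reason is also mistaken. Analysis of covariance makes its distributional assumption about residuals, not raw changes. With several hundred children per arm, large-sample or robust inference relaxes even that.

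The branch that remains uses baseline only by subtraction, makes no covariate adjustment, and does not reflect the within-nursery randomisation. The shift estimate that belongs to the test is uninformative here. At stake is how well the secondary analyses describe the size of the effect on the score. That is the scale on which the alternative hypothesis and the Background's 33–53% are expressed.

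**Working it through.** **The plan's own figure.** Rates 0.41 and 0.31, two-sided 5%, 90% power, pooled rate 0.36:

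n = [1.960·√(2·0.36·0.64) + 1.2816·√(0.41·0.59 + 0.31·0.69)]² / 0.10² = (1.3305 + 0.8652)² / 0.01 ≈ 482.1, so 483 per arm. With 40% dropout, 483/0.60 = 805. Both figures reproduce, and nothing below changes them.

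**Share with no increase.** Control 1 − 0.41 = 0.59; varnish 1 − 0.31 = 0.69; pooled 0.64. If scores never fall, these are all exact zeros, with nothing below zero and 31–41% at one tooth or more. A normal distribution is symmetric and cannot take that shape.

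**Simulation.** The document gives no mean or SD for the change, so the following are assumptions:

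- 32.98% of children have decay at baseline (the age-3 figure in Sample size).
- The chance of an increase is 1.6 times the arm average in those children, scaled so that the arm totals remain 41% and 31%.
- The increase, when present, is 1 plus a negative binomial count.
- In two scenarios, 20% or 50% of children with baseline decay and no increase fall by one tooth.

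There were 483 children per arm and 200 runs per scenario.

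| Mean increase if any | Reversals | Zeros | Largest Shapiro-Wilk p | Hodges-Lehmann = 0 | Wilcoxon power | Adjusted linear model power (robust SE) | Adjusted mean difference (teeth) |
|---|---|---|---|---|---|---|---|
| 1.5 | 0 | 64% | 9e-27 | 100% | 87.5% | 73.5% | −0.15 |
| 2.5 | 0 | 64% | 6e-28 | 100% | 87.5% | 62.5% | −0.25 |
| 4.0 | 0 | 64% | 2e-26 | 100% | 88.5% | 65.5% | −0.39 |
| 2.5 | 20% | 61% | 9e-27 | 100% | 86.5% | 70.5% | −0.26 |
| 2.5 | 50% | 57% | 4e-25 | 100% | 89.0% | 70.0% | −0.26 |

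The analysis-of-covariance branch was reached in 0 of 1,000 runs. With 200 runs, the Monte Carlo standard error of each power figure is about 2 to 3.5 percentage points.

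**Why the shift is zero.** The Hodges-Lehmann estimate is the median of all varnish-minus-control differences. Without reversals, a control child can exceed a varnish child only if the control child has an increase, so P(control > varnish) ≤ 0.41. Likewise P(varnish > control) ≤ 0.31. Both are below 0.5, so the median difference is 0. Ties at zero alone make up 0.59 × 0.69 = 0.407 of pairs.

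This does not hinge on the 41%. Take the top of the Sample size section's range, 57.63%, with the same relative reduction: varnish 0.5763 × 0.31/0.41 = 0.4357. If the increments have the same size distribution in both arms, P(control > varnish) ≤ 0.5763 × 0.5643 + 0.5 × 0.5763 × 0.4357 = 0.3252 + 0.1256 = 0.451, still below 0.5.

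**What a mean-based summary would show.** This is an illustration only. With an assumed 2.8 teeth per child with an increase in both arms, mean increments are 0.41 × 2.8 = 1.15 and 0.31 × 2.8 = 0.87, with both medians 0. The implied reduction, 1 − 0.31/0.41 = 24%, follows from assuming the same size in both arms. It is not a prediction.

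**The case against.** The Wilcoxon test is valid under randomisation and does well here: about 87–89% power in these scenarios, against about 63–74% for the baseline-adjusted linear model. Baseline is not ignored altogether, since the variable analysed is a difference from baseline. The endpoint is secondary. The primary comparison has an odds ratio with a 95% CI, and it matches the quantity that sized the trial, the proportion with new decay. All of this stands. It is why the rank test should remain the significance test.

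Three stronger readings are tempting, and the document does not support them:

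- A reader might infer that the score change will have no usable effect estimate, only two zero medians and a p-value. The section names a test and is silent on accompanying summaries. It does not forbid a mean difference with a CI, and it defers to a full analysis plan that is not shown.
- A reader might infer that the choice of method stays open until unblinding. If the switch always falls the same way, nothing is left open. The analysis plan is also to be agreed before unblinded data are seen, and nothing says normality would be judged on unblinded data.
- A reader might treat 33–53% as a firm target defined as a ratio of mean increments. The Background offers it tentatively, as a reduction in worsening of the scores. A percentage reduction in mean increment is the natural counterpart of that, but it is an interpretation.

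What the objection does not rescue is the rule itself: a condition that cannot operate, justified by the wrong criterion.

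**Conclusion.** The point holds as a fault in a stated rule for a secondary endpoint. On the protocol's own rates the normality condition will in practice not be met, and it is not the right condition for analysis of covariance with about 483 children per arm. The analysis therefore defaults to a Wilcoxon test with no stated baseline adjustment or nursery stratification, whose own shift estimate is 0 even if varnish works as planned.

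That the condition is never met is an inference from the 41% and 31%, not something the protocol states, but it held in every scenario tried. The zero shift follows from those rates alone if there are no reversals, and from simulation where some scores fall. The power figures and mean differences depend on assumed increment sizes and on an assumed link to baseline.

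The primary analysis, the sample size and the validity of the test are unaffected. This is a worthwhile correction of wording, not a threat to the trial's main conclusion.

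**What to change.** 1. Delete the normality condition.
2. For the secondary changes in both d3mft and d3mfs, keep the rank test as the significance test, stratified by nursery (van Elteren). Randomisation is already blocked within nursery. With 966 evaluable children in about 50 nurseries there would be roughly 966/50 ≈ 19 per stratum.
3. Beside it, pre-specify one estimate: the difference in mean increment from a linear model with arm, baseline score and nursery, with a robust or bootstrap 95% CI. Express it also as a percentage of the control arm's mean increment, with a CI, so that it can be set against the Background's 33% (surfaces) and 53% (teeth).
4. Do not use a negative binomial model of the 24-month score for this purpose. It gives a ratio of total scores, not of increments.

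The cost is wording only; no new data or children are needed. The downside is that on skewed data the mean-based estimate is less precise than the rank test, so its interval may include zero when the rank test is significant. The plan should say in advance that the rank test carries the significance statement and the adjusted difference describes size.

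### The 'Worst Case Analysis' scores missing children as new decay whatever their arm, which is not the worst case for the treatment comparison and makes its result depend on dropout by arm

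*Protocol article*

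**What the plan says.** All references are to the protocol article, under Statistics and data analysis.

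- **Primary comparison** (Primary efficacy analysis): "The primary analysis is the comparison between the treatment groups in percentages of children experiencing new decay as defined by the primary endpoint", that is, any increase in d3mft.
- **Analysis set** (Statistical analysis plan): children are analysed as randomised, and protocol violators are included, "provided that the 2 year endpoint data has been recorded". The main analysis is therefore of children with an observed endpoint.
- **Supplementary analysis** (same section): "We will also carry out a ‘Worst Case Analysis’ of the Primary Endpoint". The rule follows: "In this analysis the missing endpoints will be assumed to be treatment failures", with new decay given as the example of failure. It does not differ by arm, so the natural reading applies it to both.
- **Test level** (same section): "All statistical tests will be two-tailed tests at the 5 % significance level".
- **Planned loss** (Sample size): a dropout rate of 40%, described as pessimistic, from which "we would need to randomise 805 subjects in each of the two groups". No rate by arm is given.

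**The concern.** The label promises a bound, but the rule does not supply one for the quantity being tested. The least favourable assignment for varnish would count missing varnish children as decayed and missing control children as free of new decay. Giving both arms the same outcome moves both rates towards 100% by amounts set by each arm's dropout. The resulting difference therefore mixes the treatment effect with any difference in loss.

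Up to 40% of children may lack an endpoint, which is 644 of 1610. A report that the result survived a worst case would then claim more than was tested. Conversely, a sound result could appear to fail because the rule shrinks it.

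**Working it through.** **Inputs from the Sample size section.** "A two group chi-squared test with a two-sided significance level of 0.05 will have 90 % power"; the rates are "Group 1 proportion of 0.41 and a Group 2 proportion of 0.31 (an odds ratio of 1.55"; 483 evaluable and 805 randomised per arm; 40% dropout. Arm-specific dropout is not in the document. Every unequal-loss figure below is an assumption, shown as a range around 40%.

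**Step 1. Reproduce the plan's own figures.** Mean rate (0.41 + 0.31)/2 = 0.36.

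n = [1.96·√(2·0.36·0.64) + 1.2816·√(0.41·0.59 + 0.31·0.69)]² / 0.10² = 482.1, so 483 per arm. Then 483/0.60 = 805. Odds ratio (0.41/0.59)/(0.31/0.69) = 1.55. All agree with the protocol.

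**Step 2. Apply the rule.** With true rate p and missing fraction m, the scored rate is p(1 − m) + m. At m = 0.40 in both arms:

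- control: 0.41·0.60 + 0.40 = 64.6%
- varnish: 0.31·0.60 + 0.40 = 58.6%
- difference +6.0 points; odds ratio (0.646/0.354)/(0.586/0.414) = 1.29

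**Step 3. Compare with the true extremes at 40% loss per arm** (control minus varnish).

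- Against varnish: control 0.41·0.60 = 24.6%, varnish 58.6%, difference −34.0 points.
- For varnish: control 64.6%, varnish 0.31·0.60 = 18.6%, difference +46.0 points.

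The planned rule's +6.0 points lies well inside this range.

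**Step 4. Equal loss, true rates 41% vs 31%.** Two-sided pooled z test (equivalent to chi-squared), 805 scored per arm. The last column is the power of the observed-endpoint analysis with 805(1 − m) per arm.

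| Loss in each arm | Scored difference | Odds ratio | Power of this rule | Power, observed endpoints |
|---|---|---|---|---|
| 10% | 9.0 points | 1.45 | 96% | 98% |
| 20% | 8.0 points | 1.38 | 90% | 96% |
| 30% | 7.0 points | 1.33 | 81% | 94% |
| 40% | 6.0 points | 1.29 | 70% | 90% |

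**Step 5. Unequal loss, no true effect (41% in both arms).** The scored difference is 0.59 × (control loss − varnish loss).

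| Loss, control/varnish | Scored rates | Difference | Two-sided rejection |
|---|---|---|---|
| 40%/40% | 64.6% vs 64.6% | 0 | 5% |
| 41%/39% | 65.2% vs 64.0% | +1.2 points | 8% |
| 42.5%/37.5% | 66.1% vs 63.1% | +3.0 points | 24% |
| 43%/37% | 66.4% vs 62.8% | +3.5 points | 32% |
| 45%/35% | 67.6% vs 61.7% | +5.9 points | 70% |

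Excess rejections here favour varnish. Reversing the imbalance produces apparent harm at the same rates.

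**Step 6. Unequal loss, true 41% vs 31%.** With 37.5% control and 42.5% varnish loss, the difference is +2.8 points and the chance of showing benefit is about 21%. With 35% and 45%, the scored rates are 61.7% vs 62.1%, difference −0.4 points, and that chance is about 2%.

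Simulation with 200,000 replicates of the 40%/40%, 45%/35% and 35%/45% scenarios, with and without a true effect, agreed with these results.

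**The case against.** This is a supplementary analysis. No success criterion or sample size depends on it, and missing = failure is a known convention. Under equal loss it errs towards no difference and keeps its type I error. The 40% is the protocol's own pessimistic figure; at 20% loss the rule still has about 90% power. All of this stands and limits the severity.

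The design also works against unequal loss. Controls receive the same contacts and a sham application (Abstract; Visit 1/visit 2). The final examination goes ahead whatever happened to treatment (Visit 6), and it is sought for withdrawn children and leavers (Withdrawal of subjects; Unexpected end of study visit). Withdrawal after a suspected immediate reaction would fall mainly on the varnish arm, but should be rare: the Background reports 168,000 programme applications with no reported significant adverse events. A 10-point gap would be obvious from dropout by arm: 0.10/√(2·0.40·0.60/805) gives z = 4.1. It should not be treated as expected. By the same formula, however, a 2-point gap gives z = 0.8 and would pass unnoticed, though its effect is small (8% rejection).

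The opposite-assignment extremes are no cure alone. At 40% loss they span −34 to +46 points, too wide to discriminate, and they also treat imputed outcomes as observed.

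A reader might infer that the trial has no other plan for missing primary data. The document does not support that: it defers to a separate comprehensive analysis plan, which is not shown. Only the label and rule printed in the article are faulted here.

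**Conclusion.** The point holds at moderate severity. The article fixes a rule and calls it a worst case, and for the between-arm comparison it is not one. At the planning rates and 40% loss in each arm it yields +6.0 points within possible limits of −34.0 to +46.0.

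Under equal loss the consequence is attenuation only, with power falling to about 70% at the pessimistic ceiling. Under unequal loss the rule can create or hide an effect. How far it does so rests on assumed dropout by arm: false rejection runs from about 8% for a 2-point gap to about 70% for a 10-point gap.

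A reader might go further and infer that the primary result is biased by this rule or that the trial is underpowered. Neither follows: the primary analysis does not use the rule, and the 483 and 805 per arm reproduce.

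**What to change.** 1. Rename the rule 'missing = failure' and drop the worst-case label.
2. Report dropout by arm beside it.
3. Make the robustness check a delta-adjusted (tipping-point) analysis built on multiple imputation of the 2-year outcome from data already collected (baseline d3mft and d3mfs, SIMD, nursery). Vary the odds of new decay among missing children separately in each arm.
4. If a worst case is still to be claimed, report both opposite-assignment extremes.

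If the analysis plan already contains these analyses, only the protocol wording needs to change. Otherwise, settle them before unblinded data are seen, the deadline the protocol sets for agreeing that plan.

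The cost is a wording change and modest extra analysis, with no new data. The resulting robustness statement may be less favourable than one based on the present rule.
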